### Outcomes

Crestal bone levels as the primary outcome of this trial will be determined at the 1- and 3-year follow-ups by panoramic radiographs and compared with the level immediately after implant placement (Fig. 4). Implant success is the secondary outcome according to the modified criteria by Albrektsson et al. [32]: (a) implant in situ; (b) clinical immobility of the implant; (c) no evidence of peri-implant radiolucency; (d) bone loss less than 1.5 mm for the first year and less than 0.2 mm annually after the first year of service; (e) no persistent pain, discomfort or infection. The hypothesis is tested whether immediate loaded MDIs of the test group show more bone loss and less success than the MDIs of the control group.

**Fig. 4 Fig4:**
[figure not shown]
Organization chart of the trial

Tertiary outcomes arePeriodontal and peri-implant conditions (probing depths, bleeding on probing (BOP), modified plaque index, modified sulcus bleeding index (mod. SBI), tooth and implant mobility measured by Periotest and Osstell)Oral health related quality of life (measure: short German version of the oral health impact profile (OHIP-G14) [33] and Patient’s satisfaction with the PRDP (Likert scale: totally satisfied - not at all satisfied) [34]Food frequency and avoidance questionnaire will be completed by the patients to evaluate the nutrition of the patients [35]Chewing efficiency will be quantified with colour-mixing ability test using a two coloured chewing gum (optoelectronical.evaluation of the ratio of unmixed colour pixels to the total pixel number in a fixed size template) [36]Dental and prosthetic complications: tooth loss, caries, endodontic treatment, implant- or tooth fracture, prosthesis fracture, loss of retention, housing detachments, loss of O-rings.

We hypothesized that after the placement of MDIs there will be significant improvements only in group A and not in group B at the baseline and at the 4- month follow-up examination. After the pick-up of the housings in group B there will be also significant improvements for patients of this group.

Examinations for all secondary outcomes are scheduled before implant placement (pre-treatment, exclusively outcomes No.1- 4), 14 days after implant placement (baseline) and 4, 12, 24 and 36 months after implant placement (Fig. 4). In addition, patients whose housings are picked-up after 4 months will be examined 14 days after the pick-up. A trained examiner of the leading treatment center not involved in the treatment of participants will perform all examinations. Additionally, a second examiner will survey the bone levels at implants on the radiographs.

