### Randomization and blinding

The randomization was performed centrally by the trial statistician based on a sequence of computer-generated numbers with a 1:1 allocation ratio stratified by jaw (maxilla, mandible) and study center.

Due to the apparent treatment differences, it is not possible to blind the dentists, clinical investigator, and/or the participating patient. However, the two examiners of the radiographs and the statistician will be blinded.

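### One of the two radiograph readers declared blinded appears to be the clinical examiner, who normally learns the arm before the follow-up films are read

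*Protocol article*

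**What the plan says.** The Outcomes section of the protocol article makes crestal bone level on panoramic radiographs at 1 and 3 years the primary outcome, compared with the level just after placement. On who examines, it says "A trained examiner of the leading treatment center not involved in the treatment of participants will perform all examinations", and the next sentence reads "Additionally, a second examiner will survey the bone levels at implants on the radiographs". Visits are set before placement, at 14 days, and at 4, 12, 24 and 36 months. In addition, "patients whose housings are picked-up after 4 months will be examined 14 days after the pick-up".

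Randomization and blinding says that, because the treatments visibly differ, "it is not possible to blind the dentists, clinical investigator, and/or the participating patient". It continues: "However, the two examiners of the radiographs and the statistician will be blinded".

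The Interventions section describes what is visible in the early months. In group A, either housings are picked up at once or, if any implant in the jaw had a torque below 35 Ncm, the denture is relined with soft material. In group B, the recesses stay empty for 4 months, apart from an earlier soft reline in case of mucosal hyperplasia.

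**The concern.** Only two examiners are introduced. The words for the second one make sense chiefly if the first also reads the films. The first examines every patient during the months in which the denture normally shows the arm, and only later come the 1-year and 3-year films. Being outside the treating team makes this person independent, but it does not conceal the allocation.

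The stake is the primary outcome. Marginal bone level on a panoramic film is a manual measurement, and the stated hypothesis is that group A loses more bone. A reader who knows the arm can shift readings, without intent, in the hypothesised direction. The same films also feed two criteria of implant success: absence of radiolucency, and bone loss below 1.5 mm in the first year and below 0.2 mm a year afterwards. A reading shift of 0.1 to 0.2 mm is of the same order as that annual limit.

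**Working it through.** **Passages side by side**

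1. *Who reads.* Outcomes: one examiner for all examinations, plus "a second examiner will survey the bone levels at implants on the radiographs". Randomization and blinding: two radiograph examiners. The natural match is the clinical examiner and the second examiner.
2. *What the first reader sees.* At 14 days and 4 months, before any month-4 pick-up: housings or soft reline in A; empty recesses in B unless relined early for hyperplasia. Housings or empty recesses identify the arm. A soft reline points to A but does not prove it.
3. *The extra visit.* It takes place 14 days after a month-4 pick-up. Soft-relined group A patients attend it as well as group B, so by itself it does not identify the arm.
4. *When the films are read.* By 12 and 36 months both arms carry housings, so the later films need not reveal the arm. What the examiner knows comes from the early visits and matters if films can be linked to patients.
5. *What is declared.* Both readers are blinded. No sentence says how the first one is kept so.

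**Scale of a possible bias (illustration)**

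Inputs from the Sample size section: planned difference 0.4 mm, SD 0.5 mm, two-sided alpha 0.05, 26 per group for 80% power, 40 per group allocated, 75% response.

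- The plan's figure reproduces: a two-sample t-test needs 25.5, rounded up to 26 per group (power 80.7%).
- Expected evaluable patients: 40 × 0.75 = 30 per group.
- Standard error of the difference: 0.5 × √(2/30) = 0.129 mm.
- Assumption, not in the documents: the unmasked reader shifts the group difference by b = 0.1 or 0.2 mm, with no true difference.
- Shift reaching the analysed value: s = b/2 if two readings are averaged (also an assumption, since the article does not say how they are combined), or s = b if that reader's value alone is used.
- Type I error (normal approximation): 1 − Φ(1.96 − s/0.129) + Φ(−1.96 − s/0.129).

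| b (mm) | Readings used | s (mm) | s/SE | Type I error |
|---|---|---|---|---|
| 0.1 | mean of two | 0.05 | 0.39 | 6.7% |
| 0.2 | mean of two | 0.10 | 0.77 | 12.1% |
| 0.1 | that reader only | 0.10 | 0.77 | 12.1% |
| 0.2 | that reader only | 0.20 | 1.55 | 34.1% |

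This treats the analysis as a simple two-group comparison of patient means, as the sample size calculation does, not as the planned mixed model.

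**The case against.** The strongest reply is that no sentence names the clinical examiner as a film reader. The statement about all examinations follows text on visits for the other outcomes, and the blinding section contrasts the clinical investigator with the radiograph examiners, which could mean different people or masking by task. This stands in part: the overlap is a strong inference, not a stated fact.

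Second, seeing a patient at 14 days does not prevent blinded reading of a coded film a year later. The article mentions pseudonymised cases, pseudonymised planning documents and a manual of procedures, and film coding may be described in the manual or the full protocol. This also stands. A reader might infer that the blinding claim is shown to be false, but the text supports only an unresolved conflict. Equally, none of those mentions concerns masked film reading, so they do not settle it.

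Third, a reader might infer from "The randomization was performed centrally by the trial statistician" that the statistician cannot be blinded either. The documents do not support this. Additional notes promises that a statistician blinded to the groups does the calculations. That need not be the person who made the sequence, and whoever made a sequence can still analyse coded arms.

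Fourth, a reader might take 12% to 34% as the expected error rate. Those figures need the whole shift to reach the analysed value, while the second reader's blinding is not contradicted. With averaging, the same shifts give about 7% to 12%.

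**Conclusion.** The concern holds as an inconsistency between the Outcomes section and the Randomization and blinding section. On the natural reading, one of two readers declared blinded normally knows the arm from the early visits, and the article names no safeguard. The conclusion rests on two things: the inference about who the first reader is, and the absence of any stated masking of the films for that reader.

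Neither the presence nor the size of a bias can be established from the documents. The illustrative type I error is 7% to 12% with averaged readings and 12% to 34% with the clinical examiner's readings alone, for an assumed shift of 0.1 to 0.2 mm. The inconsistency does not depend on these figures. It deserves correction because it touches the primary outcome and costs little to resolve, but it does not undermine the design and falls short of a must-fix.

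**What to change.** Name the two readers and state how the films are masked. Have both read all films (after placement, 12 and 36 months) de-identified, coded without name, arm or visit date, and in random order. Re-read in this form any 12-month films already read unmasked.

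If masking of the clinical examiner cannot be assured, take the second examiner's reading as the primary bone-level value, use the clinical examiner's readings only for inter-reader agreement, and limit the blinding statement to the second examiner.

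The timing allows this. By the Recruitment section the first patient entered on 01.11.2013, so 36-month films fall due from about November 2016, after the article's publication in July 2016.

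The cost is some film handling and possibly a repeat reading of existing films, with no new reader, radiograph or visit. The fallback gives single-reader values, which are slightly less precise than a mean of two.

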### Stopping criteria

A participant will be excluded from the trial if (a) the insertion torque of one implant is <15 Ncm; (b) the patient shows intolerance/allergy to titanium; (c) the occurrence of any serious adverse events related to the implantation; (d) degradation in the health status that compromises the participation in the trial; (e) failure to comply with trial requirements; (f) the patient withdraws her/his consent. The examiner and the dentists of the treatment centers are committed to report the principal investigator on the occurrence of events promptly.

The study will be terminated if (a) more than 20 % of the implants fail in any group after implant placement; (b) recruitment will not reach 80 % of the estimated number of patients during the first year; (c) the response after the first year is < 80 % of included participants.

The criteria will be checked every six months after the inclusion of the first patient. Premature termination of the trial should be decided by principal investigator in agreement with the sponsor.

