### Interventions

Dentists of the centers with experience in dental implantology for more than ten years, who are familiar with the mini-implant system, perform the surgical and prosthetic treatment. Standard operating procedures were specified in a manual and imparted during the first calibration meeting. The first implant placement in each center was supervised by the treatment coordinator (TC) of the leading center.

Mini dental implants (MDI, 3 M ESPE, Seefeld, Germany) with lengths of 10 to 18 mm and diameters of 1.8 mm, 2.1, and 2.4 mm are used for the stabilization of PRDPs (Figs. 1 and 2). The total number of abutments per quadrant (with unfavourable distribution and number of remaining abutment teeth) will be increased to at least 3 in the maxilla or at least 2 in the mandible by the insertion of strategic MDIs (Table 1). The posterior MDI should be placed at the most posterior area of the dental arch according to the local bone volume. In the mandible, the MDIs should be located always mesial of the mental foramen. Whenever possible, the region of the canine should be occupied by an MDI (alternatively the regions of the first premolar and the lateral incisor should show abutments after intervention). If the insertion torque of one implant is < 15 Ncm due to poor bone quality the patient must be excluded from the study. Recesses for female matrices (housings) were prepared in the existing PRDP. Thereafter, a sealed envelope with the randomization detail was opened and the patient was allocated either to test group A (immediate loading/restoration) or control group B (delayed loading).

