**Fig. 3 Fig3:**
[figure not shown]
Housings for the implants presented in Fig. 2 were picked up after 4 months

Control group B (delayed loading):

The recesses for the female housings in the PRDP remained empty for 4 months. Thereafter, the housings were seated on the ball attachments and picked-up using self-cured acrylic resin (Secure hard pick-up kit, 3 M ESPE, Seefeld, Germany). In the case of mucosal hyperplasia around the implant before to the fourth months, the recesses should be relined earlier using the soft material.

During the study period and thereafter the participants will be treated by the dentists of the study sites according to their dental healthcare needs. Treatments could arise from study-related events, e.g. implant or tooth loss, prosthesis fractures or study-independent events, e. g. in the opposite jaw. Treatments before study closure will be considered as outcomes.

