### Per protocol set

We define the per-protocol by the following criteria: only one study jaw per patient; minimum number of implants as indicated in Table 1; no poor general health, no bisphosphonate therapy, no mental disorder, and no drug abuse during follow-ups; X-ray examination after 36 months is available.

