Before recruitment of study participants, the minimum number must be estimated to detect a statistically significant difference between the groups as in the present study. The sample size calculation requires assumptions that are typically cannot really be tested until the data have been collected. Sample size calculations are thus inherently hypothetical [48]. The number of additional subjects to consider dropouts over the study period is based on the experience of researchers [49]. The sample size for this trial required a multi-center design. The estimated loss to follow-up rate of 25 % is rather conservative and should also consider stopping criteria such as a low insertion torque of the MDI (<15 Ncm).

The study aims for a number of secondary endpoints including biological and technical complications, chewing efficiency and patient-based outcomes such as satisfaction and quality of life.

The chewing efficiency is measured by a mixing ability test of two-coloured chewing gum, to test the hypothesis that the additional mini-implant support of a tooth-retained PRDP improves the degree of mixing of the two colours after 20 chewing strokes [36]. For the quantitative evaluation of the flattened and scanned chewing gum specimens, a software was developed for a fast, simple and valid extraction of clinically oriented conclusions [50].

The oral health impact profile (OHIP) is a valid and reliable instrument for the measurement of the oral health related quality of life (OHRQoL) [15, 33]. A significant improvement in the OHRQoL was reported after the placement of standard-diameter implants under existing PRDPs in only one prospective study [15]. Nonetheless, there are some studies that showed some significant increase in patient satisfaction after PRDP stabilization using standard implants [10, 13, 14, 17]. In another study, distal strategic implants under PRDPs significantly improved the masseter muscle thickness and the maximum bite force [18]. The same research group further reported a particle size reduction after the chewing of silicone test cubes, and a better nutrient intake following the insertion of strategic implants [19]. Many of other studies on strategic standard implants for PRDP stabilization evaluated clinical outcomes exclusively [6–8, 11, 12, 51–53]. The 3- to 8-year-survival rates ranged between 90 and 100 % for implants and between 93 and 100 % for PRDPs.

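### The stopping criteria can take randomised patients out of the trial for reasons that may depend on loading arm, and do not separate ending study treatment from ending follow-up

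*Protocol article*

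**What the plan says.** Under Stopping criteria the article lists six reasons, (a) to (f), introduced by "A participant will be excluded from the trial if". Three matter here: (c) "the occurrence of any serious adverse events related to the implantation", (d) "degradation in the health status that compromises the participation in the trial" and (e) "failure to comply with trial requirements". None carries a time limit, and the section does not say whether an excluded patient still attends outcome visits.

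Interventions fixes the order of events. Implants are placed, torque is known and the recesses are prepared. Then: "Thereafter, a sealed envelope with the randomization detail was opened and the patient was allocated". Randomization and blinding states that dentists, clinical investigator and patients cannot be blinded; the radiograph examiners and the statistician are.

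The Discussion treats these exclusions as attrition: "The estimated loss to follow-up rate of 25 % is rather conservative and should also consider stopping criteria". The confirmatory bone-level model uses only the 12- and 36-month radiographs as the response (Primary outcome: bone level; Table 2). Additional notes rules out imputation and relies on the mixed model under missing at random. The per-protocol set, introduced by "We define the per-protocol by the following criteria", requires among other things no poor general health during follow-up and an available 36-month X-ray.

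**The concern.** Criterion (a), low torque, acts before the envelope is opened and cannot disturb the randomised comparison. Criteria (c) to (e) can act at any time up to month 36, on patients whose arm is known to those who report the events. If an event, a health decline or a lapse in compliance is connected with how the implants were loaded, the patients removed will differ between arms in a way related to outcome.

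This is a rule of conduct and not only of analysis. If the visits stop, no later choice of analysis population can supply radiographs that were never taken. The mixed model helps only where exclusion depends on data already in the model, and a patient excluded before month 12 contributes no response to the confirmatory model. Implant success at 12 and 36 months is exposed in the same way, and Kaplan-Meier implant survival would be censored for reasons that may be informative.

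**Working it through.** **Which criteria can act after allocation.** Criterion (a) depends on torque measured before allocation, so it acts before. Criteria (c), (d) and (e) have no time limit and allocation ends the implant session, so they can act after it. Some events under (c) may still fall before the envelope is opened.

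**What an excluded patient contributes, if exclusion ends follow-up.**
- Excluded before month 12: no response in the confirmatory model.
- Excluded between months 12 and 36: the 12-month value only.
- In both cases nothing is imputed.

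**Criterion (d) beside the per-protocol set.** The per-protocol filter on poor general health during follow-up has a purpose only if such patients are still being followed. Criterion (d) can take some of the same patients out of the trial. The two sections must be reconciled.

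**The plan's own figure.** Inputs from Sample size: difference 0.4 mm, SD 0.5 mm, two-sided 0.05, two-group t-test, 80% power. Standardised difference = 0.4/0.5 = 0.8. The exact t-test calculation gives 25.5, hence 26 per group, with power 80.7%. The stated 26 is reproduced. With 40 per group and 75% response, 40 × 0.75 = 30 evaluable per group, and power is 86.1%.

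**Illustration.** The documents give no exclusion rate, so the shares below are assumptions. Start from 30 evaluable per group, normal bone loss, means 0.9 and 0.5 mm and SD 0.5. Remove the fraction f of an arm with the most bone loss. The mean of those who remain is

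m − 0.5 × φ(c)/(1 − f), where c is the (1 − f) quantile of the standard normal and φ its density.

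For f = 0.05 in the test arm: c = 1.645, φ(c) = 0.103, shift = 0.5 × 0.103/0.95 = 0.054, so the difference is 0.400 − 0.054 = 0.346 mm.

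| Excluded, test arm | Excluded, control arm | Difference (mm) | Power, SD kept at 0.5 | Power, truncated SD |
|---|---|---|---|---|
| 0% | 0% | 0.400 | 86.1% | 86.1% |
| 5% | 0% | 0.346 | 73.8% | 77.9% |
| 10% | 0% | 0.303 | 61.1% | 67.4% |
| 15% | 0% | 0.263 | 48.3% | 55.5% |
| 10% | 5% | 0.357 | 74.2% | 84.8% |
| 5% | 5% | 0.400 | 84.3% | 90.9% |

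Each one-arm row removes exactly the worst patients. Exclusion unrelated to bone loss would leave the expected difference unchanged. Bias therefore needs exclusion that is both related to outcome and unequal between arms.

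**The case against.** There is a serious case on the other side, and much of it stands.

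- **The trial's bad outcomes.** A reader might infer that the rule removes the very outcomes being compared. It does not. Bone loss and implant loss are not exclusion reasons, implant failures are counted for terminating the study, and implant loss has its own survival analysis. What is at risk is the later data of patients who meet (c) to (e). Some overlap remains, since a serious infection could fall under (c) and is also a failure of the success criterion on pain, discomfort or infection.
- **Conflict with Interventions.** A reader might set the rule against "Treatments before study closure will be considered as outcomes". The examples there are implant or tooth loss, prosthesis fracture and events in the opposite jaw. None triggers exclusion, so both statements can be followed.
- **Excluded patients deleted from the analysis.** Only a per-protocol set is named, but its filters imply a wider set, and naming that set may be left to a document not shown. Nothing says that collected data are discarded.
- **Biased safety reporting.** Events must be reported promptly and are described by type, time and severity without a group comparison. An event that leads to exclusion is still on record.
- **Criterion (c) concerns surgery.** Its wording refers to implantation, which is the same in both arms. That an event under (c) depends on loading is possible but not stated; (d) and (e) are not tied to the surgery.
- **The attrition statement.** Its only example is low torque, which precedes allocation, so it is partial support for reading exclusion as the end of follow-up.

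What the objection does not remove is the rule itself: mandatory, without a time limit, applied with the arm known, and silent on continued follow-up.

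**Conclusion.** The point holds in a limited form. Followed as written, the Stopping criteria can remove randomised patients for reasons that may be connected with loading, and the missing-at-random assumption may not cover the resulting gaps. Criterion (d) also sits badly with the per-protocol filter on general health.

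The size and direction of bias are unknown. Losing the worst 5% to 15% of the test arm only would take the 0.40 mm difference to about 0.35 to 0.26 mm, with power falling from 86% to between 78% and 48% depending on the share and the SD used. That would favour immediate loading, the arm hypothesised to do worse. These figures rest on assumed one-sided exclusion of the worst patients and are not a forecast; an equal worst 5% in each arm leaves the difference at 0.40 mm. The documents do not support a claim that the comparison is already broken. This is a cheap improvement.

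**What to change.** Reword Stopping criteria so that, once the envelope is opened, meeting (b) to (e) may end study treatment but does not by itself end follow-up. Criterion (b) is included for consistency, although no bias is argued for it. Then state that:

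1. the scheduled outcome visits and radiographs are sought from every allocated patient as far as possible, unless consent is withdrawn;
2. all data already collected are kept, including those of patients who withdraw;
3. the confirmatory analyses use all allocated patients in their allocated group, and exclusions serve only to define the per-protocol set.

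Reconcile criterion (d) with the Per protocol set section so that both describe the same handling of patients whose health declines. No clinical rule is changed.

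The cost is a wording amendment and some extra effort to follow these patients. Some will be unable or unwilling to attend under (d) or (e), so some data will still be missing. By the stated dates (first patient in 01.11.2013, article published 30 July 2016), every 36-month visit still lay ahead at publication, so the change could still protect those radiographs.
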